### 2.2 Intermittent therapy

#### 2.2.1 CD4 guided treatment interruptions

The large phase III SMART trial evaluating a CD4-guided strategy of stopping ART when CD4 was above 350 cells/mm^3 and restarting when CD4 fell below 250 cells/mm^3 in adults was stopped early because of evidence of increased disease progression and cardiovascular events, albeit at low rates, in the interruption arm [23]. Treatment interruption where viral load rebound occurs is now not recommended in adults.

The PENTA 11 phase II trial (a randomised trial which compared CD4-guided PTIs versus continuous therapy in children aged 2 to 15 years) recently reported no significant increase in clinical progression in children undergoing planned treatment interruptions [22]. Further data on CD4 recovery and viral load suppression following reintroduction of continuous ART in all children in this trial are awaited and interruptions using this strategy cannot be currently recommended. However, the initial findings of PENTA 11 provided reassurance for two other paediatric trials currently investigating the impact of treatment interruptions (one evaluating interruptions following early limited ART in infants [5] and the other evaluating CD4 guided interruptions in 600 older children (BANA II trial).

### **2.2.2 Fixed length treatment interruptions**

In adults, trials of fixed length ART schedule of one week on and one week off therapy (WOWO), based on the theory of autoimmunisation [24], showed high virological failure rates in patients following the WOWO strategy compared to continuous or CD4-guided ART [25,26].

### **2.2.3 Very short treatment interruptions**

An alternative approach is to use very short interruptions (Short-Cycle Therapy) such that viral rebound should not occur, thus minimising the emergence of resistance as well as not compromising antiviral efficacy. This concept is based on the notion that >95% adherence may not be necessary for virologic suppression with all ARV regimens and that each ARV combination may have a unique adherence-resistance relationship [12]. Mathematical models of adherence and the emergence of resistance support this and the notion that otherwise strongly adherent patients might miss an acceptable number of doses of selected ARV's before resistance emerges [27].

## **2.3 Short-Cycle therapy in adults and adolescents**

Two phase II trials of SCT in adults have recently been reported. Firstly a small single-arm pilot study of 5 days on, 2 days off ART in adults in the USA showed that long-term suppression of viral load could be achieved [28]. Two of 9 patients on PI-based HAART had confirmed virological rebound by 48 weeks compared with 1/10 patients on NVP-containing HAART and 0/8 patients receiving EFV-based regimens. As a result of this pilot, the randomised FOTO (Five On Two Off) trial in 60 adults with viral load <50 c/ml on TDF/ FTC/EFV was conducted comparing daily ART to a strategy of 5 days on, 2 days off treatment. 24-week results were recently reported, showing that all 25 patients in the FOTO arm and 24 of 28 patients (86%) in the daily arm who reached week 24 had viral load <50 c/ml at this time point [29]. Reasons for not reaching 24 weeks were psychological reasons (n=2), time burden (FOTO arm) (3), pregnancy (1), and loss to follow-up (daily ART arm)(1); of note, all had viral load <50 c/ml at discontinuation. There were 6 blips (viral load 50-500 c/ml) in the FOTO arm and 9 in the daily ART arm to week 24; there were no instances of virological failure (confirmed viral load >400 c/ml).

Secondly, in a Ugandan trial [30], 171 adults who had suppressed viral load <50 c/ml on a 3-drug ART regimen were randomised to receive either a week on, week off ART regimen (n=32; this arm of the study was discontinued early), a five-days on, two-days off schedule (SCT) (n=57) or continuous therapy (n=56). The majority of subjects (94%) received an EFV-based regimen. The trial showed that SCT was not inferior to continuous HAART; there were ten cases of failure in the continuous-therapy group (plus one death) and six in the SCT group (failure defined as VL >1000 c/ml, a decrease in CD4 count from randomisation of >30% or CD4 count <100 cells/mm^3, on 2 consecutive occasions through the 72 weeks of follow-up; or at 72 weeks, VL >400 c/ml or

development of an opportunistic infection). Levels of resistance were no different in the SCT group compared to continuous group. For patients on HAART containing stavudine, there was a significant decrease in the incidence of lactic acidosis in the SCT arm compared to continuous therapy.

The USA based Adolescent Trials Network (ATN) conducted the only study of SCT to date in adolescents, which had a non-randomised single arm design to assess viral load suppression (<400 c/ml, confirmed) on SCT (4 days on HAART, 3 days off) over 48 weeks [31]. Thirty-two participants aged 12 to 24 years of age and on a stable PI-based HAART regimen for at least 12 months were enrolled. Twelve of the 32 (38%) participants had confirmed virological rebound by 48 weeks; 7 out of 15 (47%) of those infected before 9 years of age and 5 out of 17 (30%) in those infected after 9 years of age ( $p=0.5$ ). However 75% of children had been exposed to 5 or more drugs in the past, with prior history of virological failure. Overall adherence was good (88% of participants with >90% adherence) with no difference in those with or without viral load rebound ( $p=0.6$ ).

## **2.4 Antiretroviral agents, viral load rebound and resistance**

The plasma half-life of antiretroviral agents in an ART regimen (or intracellular half-life of NRTIs) and their genetic barrier to resistance are important factors which may influence viral load rebound and the development of resistance during a strategy of stopping therapy for 2 days every week. Appendix 13 gives details of the half lives of commonly used antiretroviral drugs, taken from a recent paper by Taylor *et al* [32].

An ART regimen containing three drugs, all with relatively similar long half-lives should maintain therapeutic concentrations of all 3 drugs over 2 days when treatment is stopped, avoid any risk of viral load rebound during the interruption and minimise the development of resistance. The regimen with the most favourable pharmacokinetic profile is TDF/FTC/EFV (median intracellular half-life of 150 hours, 39 hours and plasma half-life of between 36 and 100 hours respectively [32]). Co-formulation of TDF/FTC/EFV [33] in a single pill makes this a very attractive combination for older adolescents and young adults, however TDF is not yet licensed (although it is in frequent use) in children <18 years. However, in the Ugandan trial [30], EFV was given with either d4T/3TC or ZDV/3TC without evidence of inferior virological performance, even though d4T, 3TC and ZDV have shorter half-lives than TDF and FTC. Protease inhibitor drugs (e.g. Lopinavir/ritonavir (Kaletra) the most commonly used PI in children and adolescents) have substantially shorter half-lives, and therefore if a regimen containing 2 NRTIs (with longer half-lives) and a protease inhibitor (PI) (with a shorter half-life) are stopped together, "functional dual NRTI therapy" may result, with a risk of viral load rebound and the development of resistance.

Data on viral dynamics in the first few days following treatment cessation are scarce. Jacobsen *et al* in a 4-arm study of PTI  $\pm$  HIV immunisation reported viral rebound to >50 c/ml following treatment interruption at a median (interquartile range) of 15 (8 to 31) days for those with prior PTI and of 21 (13 to 30) days for those without prior PTI [24]. Harrigan *et al*, whilst assuming a constant rate of viral increase that starts as soon as the patient stops therapy, suggest that many patients stopping therapy (previously suppressed) will have increases in plasma viral HIV RNA of about 0.2 log/day and will only reach detectable levels (>50 c/ml) within 1 to 2 weeks of stopping therapy [34].

A substudy of PENTA 11 evaluated the pharmacokinetics, viral load rebound and resistance profiles in 35 children stopping non-nucleoside reverse transcriptase inhibitor (NNRTI) based ART [35]. 21 children followed a staggered stop (SS) strategy whereby the NNRTI (NVP or EFV) was stopped at randomisation and the remaining 2 NRTI drugs stopped 7-14 days later, and 14 children followed a replacement strategy (RS) whereby the NNRTI was replaced with a PI and all drugs stopped 7-

14 days later. Results of HIV viral load testing in 8 children following SS and 7 following RS strategies show that the majority of children still had undetectable HIV RNA 5-8 days after stopping all drugs (minimum 12 days after stopping the NNRTI) (Table 1). No NNRTI resistance mutations were detected in any of the children in the substudy.

**Table 1: Viral loads (c/ml) 5-8 days after 1st interruption, stopping ALL drugs in 15 children in the PENTA 11 PK substudy**

| Strategy | NNRTI | Days after stopping ALL drugs |     |                   |     |
|----------|-------|-------------------------------|-----|-------------------|-----|
|          |       | 5                             | 6   | 7                 | 8   |
| SS       | EFV   | <50                           |     |                   | <50 |
|          | NVP   | <50, <50                      | 159 | <50, 89, 7000     |     |
| RS       | EFV   |                               |     | <50               | <50 |
|          | NVP   |                               |     | <50, <50, 52, 707 | 70  |

## 2.5 Rationale and objectives

Adherence issues tend to worsen for older children and adolescents after HIV diagnosis is disclosed and the young person starts taking charge of his/her own medication; self-consciousness and not wanting to be different from peers predominates. There is the additional burden of secrecy around HIV and ART [17], and social and family pressures prevent young people from sharing information of their diagnosis or treatment with friends [36]. The result is often worsening adherence with frequently missed doses, particularly at weekends which are typically times of socialising. Factors contributing to this include alcohol ingestion [18] as well as absence of school and overnight stays with friends at weekends. Therefore a regimen where ARVs need only be taken as part of the daily routine during weekdays could be attractive for older children (>8 years) as well as teenagers and young people (16-24 years) who continue to be followed at paediatric or affiliated adolescent units.

Data from adult studies evaluating the strategy of 5 days on, 2 days off are promising with low rates of virological rebound seen. However, no randomised trial has been undertaken in older children and adolescents, a population which has potentially more to gain in terms of quality of life, long-term adherence to medication and the potential for better treatment options in adulthood. The effect on overall adherence of allowing 2 days off treatment per week is unknown and it is therefore important to first evaluate the strategy in young people who have a history of good adherence, the argument being that offering this strategy could prevent ad-hoc missed doses occurring. In view of the relatively shorter half-life of protease inhibitors and because both adult trials referred to above were undertaken with EFV-based regimens, enrolment will be limited to children who are on, or are willing to switch to, a regimen containing EFV.

This study aims to assess whether young people with chronic HIV infection undergoing Short-Cycle Therapy of five days on and two days off following complete virological response to first-line ART for at least 12 months maintain the same level of viral load suppression as those on continuous therapy. Importantly, because of insufficient data on short-term viral load rebound after stopping ART in this population, the trial will incorporate an initial pilot phase to assess the safety of the SCT strategy.

## 2.6 Risks and benefits

The potential risks of the SCT strategy are:

- The main risk is that the SCT strategy will prove ineffective in maintaining viral suppression, either because viral load cannot be maintained below detection levels during 2 days off ART, or due to non-adherence to the strategy by extending the time off treatment. However, if a raised viral load is confirmed on repeat testing (to be done within 1 week) then the participant will be placed back on continuous therapy.
- An additional risk is that young people, who have been fully adherent to ART prior to enrolment in the study, might extend the permitted very short interruptions and that overall adherence could decline. Of note, there is equipoise about whether adherence would be better or worse in the SCT arm compared with the continuous therapy arm as young people in the continuous arm may also not take their treatment regularly. All young people will be given diaries to record when they have taken ART and will be asked to comment about difficulties in remembering to take medication.  
Rebounding viral load comes with the risk of development of resistance (particularly to EFV and 3TC which have low genetic barriers to resistance) and which in turn may limit future therapeutic options. Resistance testing will be performed on all young people who lose virological suppression in either arm at the point of loss of suppression ( $\geq 50$  c/ml), as well as on any subsequent samples with HIV-1 RNA  $\geq 1000$  copies/ml.

The potential benefits of the SCT strategy are:

- Improvement in quality of life by having weekends free from taking medication.
- Improved long-term adherence during the week.
- Decreased long-term toxicity to antiretroviral drugs (particularly relevant for some NRTI drugs e.g. ZDV and TDF).
- Decreased cost which is important to any healthcare service, and in particular for many parts of the world where HIV prevalence is highest.

Young people and carers will be fully informed of possible benefits and known risks by means of a patient information sheet as appropriate and this will be reinforced by discussions with the study research teams at the individual sites prior to enrolment.

Data from the pilot phase have been reviewed by the IDMC who identified no safety concerns and recommended that recruitment continue.

## 3 SELECTION OF CENTRES/CLINICIANS

### 3.1 Clinical Sites

Sites invited to enrol young people in BREATHER will usually have previously collaborated in PENTA trials with the MRC Clinical Trials Unit, INSERM, or PHPT. In the case of a new site wishing to participate, the site will need to demonstrate sufficient resources to conduct clinical trial research with young people. MRC Clinical Trials Unit, INSERM or PHPT staff will visit new sites prior to the trial commencing at that site in order to carry out a site set-up visit. This visit should be attended by the principal investigator at that site (the clinician), the clinic nurse(s), representatives from the laboratory and pharmacy, and any other staff who will be involved in the BREATHER trial. At the trial set-up visit the trial management staff should ensure that the following minimum criteria are met before the site enrolls patients into the trial:

- The clinician should be experienced in the management of children/young people with HIV or work in close contact with a specialist HIV unit/site.
- Staff involved in the trial should have training in Good Clinical Practice (GCP)

- Pharmacy staff are able to keep detailed records of the trial medications prescribed
- There exists good communication between all of the above departments

Training will be provided for all sites participating in BREATHER. The principal investigator will sign an Investigator's Agreement for that institution on behalf of all staff at that site who will be working on the BREATHER trial. The principal investigator will sign to confirm that:

- The institution has an adequate number of qualified staff and adequate facilities for the foreseen duration of the trial to conduct the trial properly and safely.
- All staff assisting with the trial are adequately informed about the protocol, the investigational products and their trial related duties.
- The trial will be conducted in accordance with the current protocol and changes will only be made when necessary to protect the safety, rights or welfare of patients.
- The trial will be conducted in compliance with the principles of GCP and applicable regulatory requirements.
- The institution will permit monitoring and auditing by the relevant Trials Unit and inspection by the appropriate regulatory authorities. Direct access will be made available to all trial related sites, data/documents and reports.
- The institution will maintain a trial master file (TMF), which will contain essential documents for the conduct of the trial.
- All trial data will be submitted in a timely manner and as described in the protocol.
- All Serious Adverse Events (SAEs) will be reported to the relevant Trials Unit within one working day of the investigator becoming aware of the event. The initial SAE report shall be promptly followed by detailed follow up reports.
- No data on trial patients will be disclosed without the approval of the Trial Steering Committee (TSC).
- All trial related documents will be retained for at least 15 years after the completion of the trial.

In addition and in compliance with the principles of ICH GCP all institutions participating in the trial will complete a delegation log and forward this to the relevant Trials Unit. Each person working on the BREATHER trial must complete a section of this log and indicate their responsibilities. The Trials Unit must be immediately notified of any changes to trial personnel and/or their responsibilities. An up-to-date copy of this log must be stored in the TMF at the institution and also at the Trials Unit.

## **3.2 Site management**

Sites in the United Kingdom and Ireland are managed by the MRC Clinical Trials Unit at UCL. Sites in the USA, Germany, Uganda, Thailand (HIV-NAT) and the Ukraine are managed by the MRC Clinical Trials Unit at UCL in collaboration with national co-ordinators. Sites in Spain, Belgium, Denmark and Argentina are managed by INSERM SC10-US019 in collaboration with national co-ordinators. PHPT sites in Thailand are managed directly by PHPT.

# **4 DESIGN**

## **4.1 Design of Trial**

BREATHER is an open, randomised, parallel group phase II/III trial. Young people will be randomised 1:1 into two groups:

1. Continuous ART

## 2. Short-Cycle Therapy (SCT)

This is a strategy trial. Blinding of patients to the randomised strategy would not be feasible and would be inappropriate as a key objective is to improve quality of life and adherence during the week by allowing days off at the weekend.

Recruitment of a minimum of 160 young people will be over a total of 27 months. All participants will be followed until the last participant has completed 48 weeks of follow-up. Young people and/or caregivers will be asked to consent to routine clinical data being provided for two years after the main trial is complete. Further information on long term follow can be found in Section 8.10.

### Pilot Phase

The first 30 participants randomised in the study will be included in the pilot phase and will have weekly HIV-1 RNA measurements during the first 3 weeks of the study. Those randomised to the SCT arm and included in the pilot phase should stop taking their antiretrovirals on Saturdays and Sundays i.e. will follow a cycle of 5 days on ART (Monday-Friday) and 2 days off (Saturday-Sunday) during the pilot phase. Recruitment to the continuous arm will run concurrently; young people randomised to continuous ART will continue their current ART regimen\*. The IDMC will meet at the end of the pilot phase to review interim data. Recruitment will be on hold at other centres until this review has taken place.

### Main Trial

Young people randomised to SCT will follow a cycle of 5 days on ART (Monday-Friday or Sunday-Thursday) and 2 days off (Saturday-Sunday or Friday-Saturday)\*. Participants randomised to the SCT arm and included in the main phase of the trial may choose which 2 days off ART they would prefer and whichever are chosen must be continued throughout the entire time on SCT within the study. Young people randomised to continuous ART will continue their current ART regimen\*\*. Participants recruited to the pilot phase and continuing the SCT strategy can change to Friday-Saturday off in the main study.

\*Young people randomised to SCT can choose to take 2 consecutive days off during the week other than Saturday-Sunday or Friday-Saturday if these are the days that vary from their normal routine (for example, if a young person stays with a different family member on 2 days of the week then those 2 days could be the days taken off ART). The 2 days to be taken off should be decided at enrolment and should be adhered to throughout the study period.

\*\*Young people randomised to continuous ART should only stop or switch all drugs in their ART regimen for virological, immunological or clinical failure according to local practice. However if simplification of the ART regimen or substitution of one drug is deemed necessary for clinical reasons, this may be allowed after discussion with the appropriate Trials Unit.

## 4.2 Outcome measures-

### Pilot Phase Outcome Measure:

In order to examine whether SCT strategy results in an increase of viral load when ART is stopped, the pilot phase primary outcome measure is:

- HIV-1 RNA  $\geq 50$  copies/ml, reproduced on a repeat test of the same sample off ART on the Monday following SCT at any of week 1, 2, 3 (see section 11.5 for more details).

### Main Trial:

#### Primary Outcome:

In order to compare the proportion of young people with plasma RNA values  $\geq 50$  copies/ml on SCT compared to continuous ART over 48 weeks, the primary outcome of the trial is:

- HIV-1 RNA  $\geq 50$  copies/ml (confirmed on a separate sample within 1 week) at any of week 4, 12, 24, 36 or 48.

This outcome measure only considers HIV-1 RNA measurements at these time points due to the difference in viral load monitoring in the pilot phase and the main trial. However if a young person enrolled in the pilot phase has HIV-1 RNA  $\geq 50$  copies/ml at weeks 1, 2 or 3 (reproducible on the same sample) or at week 8 (confirmed on a separate sample within 1 week), they will be considered as reaching the primary outcome at week 4 and 12 respectively (see section 11.6).

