## Abbreviations and Glossary

|                                |                                                                                                                                                |
|--------------------------------|------------------------------------------------------------------------------------------------------------------------------------------------|
| AE                      | Adverse event                                                                                                                                  |
| ANRS                    | National Agency for Research (France)                                                                                                          |
| AR                      | Adverse reaction                                                                                                                               |
| ART                     | Antiretroviral Therapy                                                                                                                         |
| ARV                     | Antiretrovirals                                                                                                                                |
| c/ml                    | Copies per ml                                                                                                                                  |
| Confirmed viral load    | Viral load tested in a separate blood sample (within a week).                                                                                  |
| CDC                     | Centres for Disease Control                                                                                                                    |
| CI                      | Confidence Interval                                                                                                                            |
| CRF                     | Case Report Form                                                                                                                               |
| CTA                     | Clinical Trials Authorisation (Europe)                                                                                                         |

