## 7.7 Immunisation

If a viral load increase has occurred within two weeks of the participant having received an immunisation, the confirmatory viral load test should be performed immediately after the young person is two weeks post vaccination. The young person should go back to continuous treatment following the viral load increase and should remain on ART until the result of the confirmatory second sample is known.

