## **11.6 Analysis plan**

Intention-to-treat analyses will be performed on all randomised participants. Statistical methods include:

- Descriptive statistics for the summary of baseline characteristics
- Fishers exact test and logistic regression models for the analysis of binary outcome variables
- Analysis of variance and linear regression models for the analysis of continuous outcome variables, adjusting for baseline
- Poisson regression for the analysis of the incidence rate of clinical/adverse events
- Log rank test and proportional hazards regression models for the analysis of time to event variables

The incidence rate of clinical/adverse events will be summarised by body system and randomised arm. First events (in terms of time to first event) and all events will be considered.

Major resistance mutations will be defined by the current IAS-USA list.

The primary outcome for the main study is HIV-1 RNA  $\geq 50$  c/ml (confirmed on a separate sample within 1 week) at any of week 4, 12, 24, 36 or 48. This outcome only considers HIV-1 RNA measurements at these time points due to the difference in viral load monitoring in the pilot phase and the main trial. However if a young person enrolled in the pilot phase has an HIV-1 RNA  $\geq 50$  copies/ml at weeks 1, 2 or 3 (reproducible on the same sample) or at week 8 (confirmed on a separate sample within 1 week) they will be considered as reaching the primary outcome at week 4 and 12 respectively. All participants will be analysed in the arm to which they were randomised (intention to treat).

A full Statistical Analysis Plan (SAP) will be developed as a separate document.

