## **13.2 Ethical considerations**

- The main risk associated with undertaking this study is that the strategy will prove ineffective in maintaining viral suppression and that viral evolution with the emergence of resistance will occur. If a raised viral load is confirmed on repeat testing (to be done within

1 week) then the participant will be placed back on continuous therapy. Participants enrolled into the pilot phase should only be seen at centres where HIV-1 viral load test results are available within 2 days.

- There is the small potential risk that resistance developed during the study might render a drug or class of drugs ineffective which could in turn limit future therapeutic options. Resistance testing should be performed on all participants who lose virological suppression in either arm at the point of loss of suppression ( $\geq 50$  c/ml), and any subsequent samples with HIV-1 RNA  $\geq 1000$  c/ml.
- An additional risk is that young people, who have prior to enrolment in the study been fully adherent, might extend the permitted very short interruptions and that overall adherence could decline.
- Additional visits and blood tests are required for the trial, with intensity at the enrolment stage. If the participant is included in the SCT pilot phase, they will need to attend extra phlebotomy visits for the first 3 weeks of the trial. Those randomised to SCT arm in the main phase of trial will have only 1 viral load taken at the first week; however there are clinic visits at week 4 and 12 before resuming 3 monthly visits for all participants.
- For those participants requiring local anaesthetic cream this can be applied prior to taking blood.
- Centres will only be approached to join the trial if  $<50$  c/ml cut-off viral load assay is routinely used.
- This is a randomised trial and participants will not be able to choose which treatment approach they follow.
- This is a novel approach to ART in young people, and it is not known yet whether this is a safe strategy.

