**REPEAT on SEPARATE SAMPLE (within 1 week of VL  $\geq 50$  being reported)**

*No further weekends off until confirmatory test result known.*

[figure not shown]

**NOTE:** Participants in the CT arm should have a repeat VL on a separate sample within 1 week if any VL  $\geq 50$  is reported. If confirmed VL  $\geq 50$ , manage as per local practice

Where a VL is reported as <XX where XX > 50 (e.g. <80 copies/ml), this should be treated as a possible VL >50 copies/ml. The participant should have a repeat VL on a separate sample within 1 week to confirm if VL < 50, or a retest on a stored sample. If in the SCT arm, the participant should not continue weekends off until the repeat result is known.

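### The primary endpoint requires confirmation within 1 week, but the immunisation rule and Appendix 15 can place a protocol-compliant repeat outside that week

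*Combined protocol and SAP*

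**What the plan says.** The primary outcome in sections 1.4, 4.2, 11.2 and 11.6 is a viral load at or above 50 c/ml that is "confirmed on a separate sample within 1 week) at any of week 4, 12, 24, 36 or 48". The glossary defines a confirmed viral load in the same way: "Viral load tested in a separate blood sample (within a week". None of these places says whether the week runs from the first sample or from its result.

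Two operating rules set the timing of the repeat differently:

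- Appendix 15, for the main trial and long-term follow-up: "REPEAT on SEPARATE SAMPLE (within 1 week of VL $\geq 50$ being reported". Here the week starts at the report.
- Section 7.7, for a rise within two weeks of an immunisation: "the confirmatory viral load test should be performed immediately after the young person is two weeks post vaccination".

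On turnaround, section 13.2 says that pilot participants "should only be seen at centres where HIV-1 viral load test results are available within 2 days". I found no limit for the main trial.

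Sections 4.2 and 11.6 also state an exception for the pilot. A participant reaches the primary outcome with a value at or above 50 "copies/ml at weeks 1, 2 or 3 (reproducible on the same sample) or at week 8 (confirmed on a separate sample within 1 week"; the week 1 to 3 events are counted at week 4 and the week 8 events at week 12.

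Section 11.6 leaves the full SAP to a separate document. In the text available I found no rule for scoring a repeat that is late, missing or delayed by immunisation. The Appendix 15 chart itself is not reproduced.

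**The concern.** A site can do exactly what section 7.7 or Appendix 15 asks, obtain two consecutive values at or above 50 c/ml on separate samples, and still have a pair that fails the written endpoint if the week is counted from the first sample. The participant would then be scored as suppressed unless a later scheduled visit produced a pair that met the window.

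The direction matters. Section 11.3 sets up a non-inferiority comparison with a 12-point margin, and losing the same fraction of true failures from both arms shrinks the difference between them. The trial is open (section 4.1), so if the rule is not written down, doubtful pairs may be resolved with allocation known.

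**Working it through.** **1. The plan's own figure.** Inputs from section 11.3: 90% suppression in both arms, margin 12 points, one-sided alpha 0.05, power 80%. Total = 2 × (0.90×0.10 + 0.90×0.10) × (1.645 + 0.842)² / 0.12² = 154.6. This reproduces the stated 155; allowing for 3% loss gives 160. The design arithmetic is not in question.

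**2. Immunisation delay.** For a rise on day d after the vaccine, with the repeat drawn on day 14, the gap between samples is 14 − d.

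| d | 0 | 4 | 5 | 6 | 7 | 10 |
|---|---|---|---|---|---|---|
| gap (days) | 14 | 10 | 9 | 8 | 7 | 4 |

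Rises on days 0 to 6 always give a gap of 8 to 14 days. From day 7 the repeat can fit within a week of the sample.

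**3. Appendix 15.** With turnaround t, a compliant repeat can fall up to 7 + t days after the first sample.

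- t = 2 (the pilot-centre limit): repeats made 1 to 7 days after the report fall on days 3 to 9. Those made 1 to 5 days after the report are within a week of the sample; those on days 6 and 7 are not.
- t = 7 (assumed, for range): repeats fall on days 8 to 14, all outside.

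Starting the week at the report does not by itself settle section 7.7. The repeat is then in time only if 14 − d ≤ 7 + t, that is d ≥ 7 − t. With t = 2, rises on days 0 to 4 still miss the window.

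**4. How few events matter.** The one-sided 95% upper limit for the difference in failure is (p2 − p1) + 1.645 × √[p1(1−p1)/n + p2(1−p2)/n]. This Wald form is my choice, because section 11.6 does not name the interval. Event counts are illustrative.

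- 8/80 in each arm: upper limit 7.8%.
- 8/80 against 11/80: 3.75 + 1.645 × √(0.0900/80 + 0.1186/80) = 3.75 + 8.40 = 12.15%, above the margin.
- At 110 per arm, 11 against 16 gives 11.8% and 11 against 17 gives 12.8%.

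Starting from equal arms, rescoring three SCT participants (80 per arm) or six (110 per arm) changes the conclusion.

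**5. Illustration of the bias.** Assume true failure of 10% on continuous therapy and 22% on SCT (at the margin), and that a fraction q of true failures in both arms is scored as suppressed. The apparent difference is 12 × (1 − q) points. False non-inferiority comes from exact binomial enumeration of the rule in step 4.

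| q (assumed) | apparent difference | 80 per arm | 110 per arm |
|---|---|---|---|
| 0 | 12.0 | 5.4% | 5.2% |
| 10% | 10.8 | 8.3% | 8.6% |
| 20% | 9.6 | 12.9% | 14.1% |
| 30% | 8.4 | 19.7% | 22.5% |

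No value of q can be derived from the documents, and the table allows nothing for failures picked up at a later visit.

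**6. The pilot exception.** Section 11.5 treats up to 4 same-sample events among 15 SCT participants as compatible with continuing. If all 4 lacked separate-sample confirmation, they would add 4/80 = 5.0 points or 4/110 = 3.6 points to SCT failure. That works against SCT, the opposite direction to step 5.

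**The case against.** The strongest reply is that Appendix 15 does not contradict the endpoint. The endpoint names no start for its week and Appendix 15 supplies one. A participant cannot be recalled before the result exists, so it reads naturally as the working definition, and then every repeat that complies with it counts. That is a fair reading, and a reader who infers an outright contradiction goes further than the text. But the reading is nowhere written down, and step 3 shows that it does not clear the section 7.7 cases when turnaround is short.

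Second, the documents do not say that a late repeat is scored as suppressed; they are silent. The separate SAP may set windows, the glossary lists an Endpoint Review Committee, and section 12.3 has primary-endpoint viral loads checked against source. Some missed rebounds would also be caught at later scheduled visits, and suppression at weeks 24 and 48 is a secondary outcome with no confirmation requirement. All of this stands and limits the likely damage. None of it supplies the missing rule.

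Third, the immunisation problem is narrow. It covers rises on days 0 to 6 only, and nothing says how many participants are vaccinated shortly before a scheduled visit. That stands.

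Fourth, a reader might infer that the pilot same-sample rule is another inconsistency, since section 7.2 lets a participant whose week 2 separate sample is below 50 take a further interruption although the endpoint is already scored as reached. The documents do not support calling this an error. Sections 4.2 and 11.6 disclose the exception within the endpoint definition, tie it to the different pilot monitoring and apply it to both arms. Pilot SCT samples are taken off drug on a Monday and continuous-arm samples at any time in the week (section 1.5), so any excess is likely to fall on SCT, which is conservative for non-inferiority. Replacing the rule would be a trade-off: off-drug rises would be overruled by a repeat taken after a weekend on treatment. Large pilot effects are also hard to square with the record. A 15% per-sample rate would imply 15 × (1 − 0.85³) = 5.8 events, above the level of 5 that section 11.5 calls concerning, whereas sections 2.6 and 11.4 report that the IDMC found no safety concerns.

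**Conclusion.** The point holds in this form. The endpoint's one-week condition and the plan's own instructions for the repeat do not fit together: section 7.7 makes a repeat within a week of the sample impossible for rises on days 0 to 6 after a vaccine, and Appendix 15 allows a repeat up to 7 days plus turnaround after the sample. On a literal reading, genuine repeated rebounds handled according to protocol can be scored as suppressed, and that error favours non-inferiority.

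The frequency is unknown. The rise in false non-inferiority to 8-20% (80 per arm) or 9-23% (110 per arm), against about 5%, rests on an assumed loss of 10 to 30% in both arms, true failure of 10% and 22%, a Wald limit and no recapture. A reader might take those figures as the expected bias; they show only how sensitive the conclusion is. The immunisation conflict is the firmest part. The Appendix 15 part depends on how the unstated start of the week is read.

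**What to change.** For endpoint scoring, redefine confirmed in the glossary and sections 1.4, 4.2, 11.2 and 11.6: the repeat that the protocol directs, on a separate sample, is also at or above 50 c/ml. State that this includes repeats timed from the report under Appendix 15 and repeats delayed under section 7.7. Keep 1 week as an operational target, not as a condition of the endpoint. Sections 4.2, 7.7 and 11.6 and Appendix 15 must be reconciled; which timing is clinically right is for the investigators and is not proposed here.

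Keep the disclosed pilot same-sample rule in the primary analysis. Add two sensitivity analyses: one that excludes pilot events not confirmed on a separate sample, and one that counts a rise with no repeat as an event.

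The cost is a wording change and two extra analyses; sample size and visits are unchanged. The downside is slightly looser confirmation timing. Version 1.10 is dated May 2015 and section 1.13 places the final long-term visits in April to July 2016, two years after the main trial, so the 48-week data were probably already collected. The definition should therefore be recorded, with its date, without reference to event counts by arm.
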